### Eligibility criteria for selection and training of pharmacists

An eligibility criterion has been outlined for pharmacists who would participate in the study. The minimum requirements for a pharmacist to be eligible to participate in the study and to be able to deliver the intervention were layed out. The applicant would be a graduate with Doctor of Pharmacy, i.e., Pharm.D degree obtained from an institute recognized by the Pharmacy Council of Pakistan [18]. The applicant should be registered as ‘Pharmacist’ in category, ‘A’, by the pharmacy regulatory body [19]. The registration certificate should be valid at the time of applying for participating in this study.There are two types for bachelor’s degrees awarded to pharmacists in Pakistan. The Bachelor of Pharmacy, i.e., B.Pharm and Doctor of Pharmacy, i.e., Pharm.D. The B.Pharm is a four-year degree while Pharm.D is relatively new degree that is completed over a course of five years with a residency component if the candidate wants to pursue a career in health sector. The Pharm.D degree has more clinically oriented courses and students learning is enhanced through clinical rounds [20]. Therefore, Pharm.D graduates would be included. The registration by regulatory body is important as it would be required in clinical practice. All applicants who lack in any of the abovementioned criteria would be excluded from study.The pharmacists involved in the study will be trained. A total of eight lectures of 1-h duration is planned over a span of 2 weeks to be given to participating pharmacists. These lectures will focus on selected topics on RA disease that are deemed important and helpful while educating patients. These will include disease epidemiology in Pakistan, symptoms and risk factors, brief information about diagnosis and treatment, the importance of physical therapy and rehabilitation, the importance of adherence to treatment and self-care techniques. Training will also include a lecture on the pharmacist’s role in self-care and home-based disease management and a lecture to reinforce patient counselling skills for pharmacists. The training will also encompass detailed briefing on the study protocol and administering the intervention. The training module and disease education literature will be provided to all pharmacists for the purpose of self-study at home. An assessment test based on the lectures will be conducted at the end. The training presentation is available as Additional files 4 and 5. Disease education literature for patients is available as Additional file 6.

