
### Intervention

The intervention consists of a pharmacist providing pharmaceutical care that will be in the form of an educational intervention. It will be delivered by the pharmacist as a single, face-to-face, structured session of 20–25 min duration. Moreover, specially designed RA disease education literature will be provided in both the Urdu and English languages for patients to use at home. An intervention delivery plan consisting of a checklist has been developed to assure uniformity of the intervention delivered to patients. The plan is available as Additional file 7.

A specially designated counselling area in the rheumatology clinic serves as a venue for the intervention. The schedule of enrollment, intervention and assessment is provided in Fig. 2. The implementation will be observed by utilizing mixed models with random intercepts for pharmacists. The variance fraction explained will be observed by calculating the intraclass correlation coefficient using unconditional and conditional models [21].

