##### Direct cost of treatment

The mean direct cost of RA treatment after 3 months (week 12) from baseline (week 0) will be calculated in patients enrolled in the CG and in the IG. We consider direct cost of treatment as the cost incurred for appointments with rheumatologists, follow ups, medications and rehabilitation/physical therapy, aimed at minimizing any disease-related impairment [25, 26]. This will be documented using a specially designed data collection form.

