### Statistical analysis

The statistical analysis will be conducted by a statistician who will be blinded to patient-group allocation. The analysis will be carried out using SPSS version 22 (IBM SPSS, Armonk, NY, USA). The analysis will consist of a per-protocol set that includes participants who have completed the study as per the defined protocol. The significance level will be set at 5% and a two-tailed test will be used. Continuous data will be descriptively analysed using the Mann-Whitney U test, while the chi-square test will be used to analyze categorical variables by comparing them in the two groups at the same time point. Confirmatory analysis will be carried out using the Wilcoxon signed-rank test to analyze differences in the mean values for disease knowledge, adherence to treatment and medications and the cost of treatment after 3 months, i.e., baseline within-subject analysis. Multinomial logistic regression will be used to interpret the odds ratios for the secondary outcome, i.e., patient satisfaction with pharmacist counselling. There will be no interim data analysis.

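### The confirmatory cost analysis is a within-patient rank test, so it tests neither mean cost nor a difference between arms, and the cost items exclude the intervention without a stated costing perspective

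*Protocol article*

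**What the plan says.** Under Direct cost of treatment, the protocol article sets the summary measure for both arms: "The mean direct cost of RA treatment after 3 months (week 12) from baseline (week 0) will be calculated". The Abstract and the Discussion describe the outcome as the change in mean direct cost. The content is a list: "We consider direct cost of treatment as the cost incurred for appointments with rheumatologists, follow ups, medications and rehabilitation/physical therapy".

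The Statistical analysis section then states: "Confirmatory analysis will be carried out using the Wilcoxon signed-rank test to analyze differences in the mean values". The variables covered are knowledge, adherence "and the cost of treatment after 3 months, i.e., baseline within-subject analysis". For comparisons between groups it states: "Continuous data will be descriptively analysed using the Mann-Whitney U test".

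The Intervention section gives intervention patients a "single, face-to-face, structured session of 20–25 min duration", plus printed education material. The section on pharmacist training adds: "A total of eight lectures of 1-h duration is planned over a span of 2 weeks". None of these three resources is among the listed cost items.

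No costing perspective is named. The Discussion justifies the cost outcome by the financial burden on the patient; the closing paragraph of the Background speaks of the burden on society.

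**The concern.** The secondary objective is the effect of the intervention on the cost of treatment. In a randomized trial that effect is the difference between arms, and the article expresses it in means. The analysis given confirmatory status uses no control data and ranks the changes instead of averaging them.

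Two things follow. Any cost change over 12 weeks that both arms share would count as a positive result in the intervention arm. And if a few patients incur large extra costs while most save a little, the ranks and the mean can point in different directions.

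Separately, a cost figure that leaves out the service being tested cannot show what the service does to the payer's budget. A reader who takes the article's remark about future delivery of care in Pakistan as referring to cost could read the figure that way.

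**Working it through.** **Inputs.** The article states no expected cost, SD or cost difference, so there is no plan figure to reproduce. Only the number of patients comes from the document (Sample size): 619 in total, 20% dropout, 1:1 allocation. Completers: 619 × 0.8 = 495, about 247 per arm. Randomized to intervention: about 310. Every cost value below is an assumption for illustration, on a scale where mean cost is 100.

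**1. What each test addresses.**

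| | Uses both arms | Tests a mean | Status in the plan |
|---|---|---|---|
| Outcome as defined | yes | yes | secondary outcome |
| Wilcoxon signed-rank | no | no | confirmatory |
| Mann-Whitney U | yes | no | descriptive |

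No planned test matches the outcome on both counts.

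**2. No control arm in the confirmatory test.** Suppose cost falls by 10 in both arms, so the intervention effect is zero, and changes are symmetric with an SD of 60. The signed-rank test then behaves much like a paired t-test. SE = 60/√247 = 3.82; 10/3.82 − 1.96 = 0.66; the chance of a significant fall in the intervention arm is about 75%. With an SD of 100: SE = 6.36; 10/6.36 − 1.96 = −0.39; about 35%.

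**3. Ranks against means, exact case.** Suppose 95% of intervention patients cost 10% less and 5% cost four times as much. The mean ratio is 0.95 × 0.90 + 0.05 × 4 = 1.055, a rise of 5.5%. Among 247 patients about 12 rise. If those 12 hold the largest ranks (236 to 247), the positive rank sum is 12 × 241.5 = 2,898. Under the null it is 247 × 248/4 = 15,314, with SD √(247 × 248 × 495/24) = 1,124. So z = (2,898 − 15,314)/1,124 = −11.0: a decisive fall by ranks while the mean rises.

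**4. How far that depends on the data.** Simulations with 247 per arm, some also with 309:

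- Same 95/5 scenario with added within-patient variation between visits: signed-rank reports a fall in about 43–53% of runs at a within-patient log-SD of 0.3, and 10–13% at 0.5.
- Same scenario, Mann-Whitney on lognormal costs: significantly lower intervention cost in about 74%, 22%, 9% and 7% of runs at log-SD 0.3, 0.5, 0.8 and 1.0.
- Equal arm means of 100, more skew in the intervention arm (log-SD 0.8 against 1.1, or 1.0 against 1.3): Mann-Whitney points to lower intervention cost in 89–95% of runs; a Welch t-test is significant in 5–6%.
- Mean change zero, 90% save 10 and 10% spend 90 more (noise SD 5): signed-rank reports a fall in 100% of runs; a t-test is significant in 5–6%.
- Mean change zero, milder skew (70% save 10, 30% spend 23.3 more, noise SD 20): signed-rank reports a fall in about 6%.

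**5. The omitted resource.** Session time: 310 × 20/60 = 103 hours to 310 × 25/60 = 129 hours across the trial, that is 20–25 minutes per patient, plus literature and eight lecture hours per pharmacist. The article gives no wage or unit cost to turn this into money.

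As a range only: suppose the session costs c per patient and the measured saving is also c, so the net effect is zero. The chance of a significant measured saving in a test of means is Φ(c/(SD × √(2/247)) − 1.96). For c = 10 and SD 60: 10/5.40 − 1.96 = −0.11, giving 46%.

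| Omitted cost c | 2 | 5 | 10 | 15 | 20 |
|---|---|---|---|---|---|
| SD 60 | 6% | 15% | 46% | 79% | 96% |
| SD 100 | 4% | 8% | 20% | 38% | 60% |

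The document does not say which column applies, or whether patients pay for the session.

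**The case against.** **Perspective.** A reader might infer that leaving out the session biases the cost outcome towards the intervention. The documents do not support that without qualification. The one reason the Discussion gives for the cost outcome is the patient's financial burden, and from that viewpoint an uncharged session costs nothing and its omission creates no false saving. The listed items are items of arthritis care, and no net-cost or cost-effectiveness analysis is promised. This stands, but only as far as it goes: the Background also invokes society, and the article settles neither the perspective nor whether anyone is charged. The inference holds for a provider, health-system or societal reading and not otherwise.

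**Direction.** Medication and physical therapy are counted costs, and better adherence could raise both. Nothing in the protocol predicts a saving. This stands.

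**Visibility.** Mean cost will be calculated in both arms, so a conflict between ranks and means would be seen. That is true, but seeing a conflict does not supply a valid test of the difference in means.

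**Dependence on assumptions.** The reversal in step 3 weakens as costs vary more, and the eligibility criteria exclude some patients likely to have extreme costs. This stands: a reversal is possible, not inevitable.

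**Scope.** The within-patient confirmatory test also covers knowledge and adherence, so the defect is not confined to cost. That does not excuse it here, and the mean matters particularly for a cost outcome.

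**Conclusion.** The point holds in two parts.

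The first rests on the text alone: the outcome is a mean in each arm, while the confirmatory test is within patients and based on ranks. This is a rule stated wrongly, not a detail left to a fuller document. A before-after fall in the intervention arm could be reported as confirmed with no comparison with controls. How often ranks and means would disagree depends on a cost distribution the article does not describe; the assumed cases run from about 6% to 100%.

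The second is narrower. The cost list excludes resources used only by the intervention arm, and no perspective is stated, so the result could be misread as a net saving. The size of this omission cannot be determined from the document.

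A reader might go further and conclude that the trial will report a saving that does not exist. The documents do not support that: the direction of the cost effect is open, the rank-mean conflict is conditional, and the omission matters only under some perspectives. The analysis should be changed, but no false result has been shown.

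**What to change.** - Make the cost analysis the between-arm difference in arithmetic mean direct cost at week 12, adjusted for baseline cost, with a bootstrap 95% confidence interval or a gamma GLM. The Study plan records the same data at both visits, so no new patient data are needed.
- Drop the signed-rank test as the confirmatory cost analysis. It may remain as a description of change within each arm.
- State the costing perspective. Then either report cost with and without the session, literature and a share of training, or label the outcome as patient treatment cost excluding the intervention.
- Trial status says that recruitment has closed and results are being analysed. The change should therefore be dated and disclosed in the report.

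The price is one further analysis and, if the intervention is costed, a small unit-cost calculation using wage and printing figures that the article does not contain. The cost result may become less favourable to the intervention.

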##### Patient satisfaction

Patient satisfaction resulting from pharmacist-led pharmaceutical care will be assessed using a form for “Patient satisfaction feedback (PSF) on counselling” [27]. The proportion (percentage) of patients in the IG who were satisfied with the intervention after 3 months (week 12) from baseline (week 0) will be calculated.

### Feasibility assessments

In this trial we will have continuous assessment through designated health officials from hospital staff who would act as independent observers. These observers will be supervised by a designated member of the ethical review committee. Moreover, the committee will be updated separately by the officials and by the investigators on trial progress. This continuous assessment of trial progress will ensure three-tiered compliance of the study as per the approved protocol. The process will be assessed, i.e., the randomization process, blinding of data assessors, monitoring and management of data and the effectiveness, safety or any ethical issues pertaining to the intervention. The assessment of the study process will further help evaluate if the patients are properly briefed about the study and if the eligibility criteria need to be modified. Moreover, it will oversee the recruitment process as well as measures that are needed in case a patient withdraws his/her consent. Secondly, the assessment of study resources will encompass evaluation and/or modification in the numbers of materials used to document data that include stationery, computers, rooms, facilities, human resource and logistics. The data assessment will ensure proper data collection, data entry into the software and its validation. The assessment will also ensure blindness to allocation during data collection and analysis.

### Sample size

Few randomized controlled trials have evaluated the effect of pharmacists’ educational interventions on adherence and disease knowledge among patients with RA. We reviewed several studies that could serve as a reference for calculation of sample size based on treatment effect. A study conducted by Clifford and colleagues assessed the effect of pharmacist educational advice on improving adherence [7]. Another study by Stockl and colleagues was nonrandomized and was limited to evaluating the effects of a telephone intervention by either a pharmacist or a nurse, on patients’ adherence to injectable RA medicines [8]. Azzopardi and colleagues used a different outcome measure to ours and included patients with RA prescribed methotrexate only [28]. Similarly, in another RCT, Petkova measured a different outcome [3].

We considered a study by Clifford and colleagues as a standard and calculated our sample size based on the primary outcome, i.e., adherence [7, 29]. It was taken as a reduction in self-reported nonadherence from 16% to 9% considering a (two-side) alpha value of 0.05 and statistical power of 80%, i.e., beta = 0.2. Considering a drop-out rate of 20%, we would require a total of 619 patients to successfully demonstrate a positive and statistically significant effect.

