**Methods/design:**

This is a randomized, single-blind, two-arm, controlled trial in patients with rheumatoid arthritis visiting outpatient rheumatology clinics in Karachi, Pakistan. We will enroll patients with established diagnosis of rheumatoid arthritis over 3 months. The patients would be randomized through a computer-generated list into the control group, i.e., usual care or into the intervention group, i.e., pharmaceutical care, in a ratio of 1:1, after providing signed written consent. The study will take place in two patient-visits over the course of 3 months. Patients in the intervention group would receive intervention from the pharmacist while those in the control group will receive usual care. Primary outcomes include change in mean score from baseline (week 0) and at follow up (week 12) in disease knowledge, adherence to medications and rehabilitation/physical therapy. The secondary outcomes include change in the mean direct cost of treatment, HRQoL and patient satisfaction with pharmacist counselling.

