Evidence from several randomized trials indicate that pharmacist-driven patient counselling, consultation, disease education and advice, as well as telephonic intervention, have improved patients’ self-care. Educating patients about managing RA empowers them in understanding signs and symptoms of disease and devising ways to reduce or limit aggravating factors. A randomized trial conducted by Petkova that involved a community, pharmacy-based, patient education program and demonstrated improved treatment outcomes in patients with RA [4]. Moreover, Mary and colleagues demonstrated a positive effect of a mobile phone short message service on medication adherence in patients with RA [5]. A systematic literature review by Leville and colleagues highlighted the role of the pharmacist as an adviser on issues related to medication management. The intervention performed by pharmacists has shown improvement in patients’ adherence to medication not only in rheumatological conditions but also in other chronic illnesses [6, 1]. Another randomized controlled trial (RCT) by Clifford and colleagues reported a significant drop in non-adherence to medication and in the incidence of medication-related problems after a 4-week follow up. This improvement was reported in patients with RA who had telephone intervention delivered by the pharmacist [7]. Moreover, Stockl and colleagues reported improved adherence to medication in patients with RA who had telephone consultations with the pharmacist [8].

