### Randomization and allocation concealment

Patients will be randomly allocated to one of the two treatment groups using a randomization ratio of 1:1. The technique used will be simple randomization using a computer-generated list. The participants’ medical record numbers will be entered into the hospital’s software and a list of appointments will be generated with patients designated into the CG or the IG.

Allocation will be automatically concealed through the computer-generated list, which automatically allocates a clinic room number. For instance, if the computer enrolls a patient into the IG, it generates the appointment slip with a clinic room number in which a pharmacist will provide the intervention and vice versa. There are two room numbers, i.e., 1 = without pharmacist intervention and 2 = with pharmacist intervention. The patients and data collectors will be unaware of this number scheme. Patients in the CG will go to clinic room 1 and have their consultation with rheumatologist. The pharmacist will not provide the intervention. Before consultation, the patients will go to a consultation room where a data collector will wait with a data file printed on yellow-colored paper. If the computer enrolls a patient into the IG, the appointment slip will be printed with clinic room number 2. Patients in the IG will go to that clinic room where the rheumatologist and a pharmacist await them. The patients will undergo the intervention after consultation with the rheumatologist. Similarly, before the intervention, patients will enter a consultation room where the data collector will wait with a patient data file printed on white paper. The data collector and pharmacist will be unaware of the color scheme. Therefore, the pharmacist will be unaware of outcome assessment.

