### Outcomes

#### Primary outcome measurements

##### Treatment adherence

There are two modes of assessing treatment adherence, i.e., medication adherence and rehabilitation/physical therapy adherence. Both modes will be assessed after 3 months (week 12) from baseline (week 0). The Urdu version of the General Medication Adherence Scale (GMAS) [1] will be used for the assessment of adherence to medication and pharmacotherapy. The scale consists of eleven items that measure a patient’s adherence to medication and provide a score that could be interpreted as high, good, partial, low or poor adherence. There are four possible choices for each item, i.e., always, mostly, sometimes or never, which give a score of 0, 1, 2 or 3, respectively [22]. Adherence to rehabilitation/physical therapy will be assessed by utilizing the Urdu version of the General Rehabilitation Adherence Scale (GRAS). The scale consists of eight items that measure a patient’s adherence to physical therapy and provide a score that could be interpreted as high, good, partial, low or poor adherence. There are four possible choices for each item, i.e., always, mostly, sometimes or never, which give a score of 0, 1, 2 or 3, respectively ([name]: Development and validation of General Rehabilitation Adherence Scale (GRAS) in patients undergoing physical therapy for various musculoskeletal diseases. (unpublished work).

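### The stated 80% power belongs to a comparison of two nonadherence proportions, not to any confirmatory test of the score-based primary outcomes, and 619 patients do not give 80% for the proportions either

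*Protocol article*

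**What the plan says.** All references are to the protocol article.

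- **Sample size.** The authors "calculated our sample size based on the primary outcome, i.e., adherence". The effect is a difference in proportions: "It was taken as a reduction in self-reported nonadherence from 16% to 9"%. The error rates are then fixed in these terms: "considering a (two-side) alpha value of 0.05 and statistical power of 80%, i.e., beta = 0.2". The total follows: "Considering a drop-out rate of 20%, we would require a total of 619 patients".
- **Abstract, Methods/design.** "Primary outcomes include change in mean score from baseline (week 0) and at follow up (week 12) in disease knowledge", and likewise in adherence to medication and to rehabilitation or physical therapy. The Discussion repeats that all three primary outcomes are changes in mean score.
- **Outcomes, Treatment adherence.** GMAS has eleven items and GRAS eight, each item scored 0 to 3. Both scales "provide a score that could be interpreted as high, good, partial, low or poor adherence". No cut between adherent and nonadherent is given.
- **Statistical analysis.** The confirmatory analysis is a Wilcoxon signed-rank test of change from baseline within subjects. Between-arm tests are also listed (Mann-Whitney for continuous data, described as descriptive, and chi-square for categorical data), but neither is called confirmatory.
- **Randomization and allocation concealment.** Allocation is 1:1.

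**The concern.** A power figure is a property of one test on one endpoint. Here the figure comes from comparing two independent proportions, while the trial's claims will rest on scores. Two things differ: the type of endpoint (event versus mean score change) and the comparison (between arms versus within subject). The article does not say how 16% or 9% would map onto GMAS or GRAS, or which of the two adherence scales was sized. RAKAS has no sizing at all.

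At stake is how the result is read. A null finding on GMAS, GRAS or RAKAS would be set against an 80% that does not describe it, and the reader is not told what score difference the trial could detect.

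**Working it through.** **Inputs.** From Sample size: p1 = 0.16, p2 = 0.09, two-sided alpha 0.05 (z = 1.960), power 0.80 (z = 0.842), dropout 20%, N = 619. From Randomization and allocation concealment: 1:1. The article gives no SD or expected mean difference for any scale.

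**1. Reproducing 619.** Two proportions, pooled variance under the null, mean proportion 0.125:

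n per arm = [1.960 × √(2 × 0.125 × 0.875) + 0.842 × √(0.16 × 0.84 + 0.09 × 0.91)]² / 0.07² = [0.917 + 0.391]² / 0.0049 ≈ 350

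The total is 700, and 700 / 0.8 = 875. Other conventions:

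| Method | Total before dropout | Total after dropout (N/0.8) |
|---|---|---|
| Two-sided, pooled | 700 | 875 (840 as N × 1.2) |
| Two-sided, unpooled | 693 | 867 |
| Two-sided, arcsine | 688 | 860 |
| Two-sided, continuity-corrected | 756 | 945 |
| One-sided, pooled | 550 | 688 (660 as N × 1.2) |
| One-sided, continuity-corrected | 606 | 758 |

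The nearest figure is 606, which is one-sided and has no dropout allowance. No variant tried that keeps the two-sided test and the 20% dropout gives 619.

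**2. Power of 619 for 16% versus 9%.** Evaluable after dropout: 619 × 0.8 = 495.2, or 247.6 per arm.

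Power = Φ{[0.07 × √247.6 − 0.917] / 0.465} = Φ(0.397) ≈ 65%

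Here 0.465 is √(0.16 × 0.84 + 0.09 × 0.91). If all 619 were evaluable, power would be about 75%.

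**3. What 495 evaluable patients can detect on a score.** Two-sided 5%, 80% power, 247.5 per arm, in SDs of whatever variable is analysed:

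- Between-arm difference in means: (1.960 + 0.842) × √(2/247.5) = 0.252 SD.
- Mann-Whitney with normal data (relative efficiency 0.955): 0.252 / √0.955 = 0.258 SD.
- Between-arm means with alpha split over three outcomes (0.05/3, z = 2.394): (2.394 + 0.842) × √(2/247.5) = 0.291 SD.
- The confirmatory test as written, paired within one arm (normal approximation): (1.960 + 0.842) / √247.5 = 0.178 SD of the change score. This concerns change within an arm, not the difference between arms.

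**4. Which SD.** SD of change = SD of score × √(2(1 − r)), where r is the correlation between baseline and week 12. The two are equal only at r = 0.5, so 0.25 SD has no meaning in points until the SD is named and sourced.

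**The case against.** **The trial does plan a between-arm categorical test.** The chi-square test could be applied to adherence categories, and a cut may exist in the scale's scoring source or the full protocol. This stands in part: it would be wrong to say that no such comparison could be made. But the test is not called confirmatory, the article dichotomises nothing, and categorised adherence is not a listed primary outcome.

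**No harm is shown.** This stands. A reader might infer that the score analyses are underpowered, and the document does not support that. If nonadherence were the tail of a normal score with equal SDs (an assumption), 16% versus 9% would be a shift of 1.341 − 0.994 = 0.35 SD. With 247 per arm, a between-arm comparison of means would then have about 97% power, or about 93% at alpha 0.05/3. On that assumption the scores are better powered than the proportion.

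**A detectable difference worked back from 619 is not a justification.** This also stands. It does not show that 0.25 SD matters to patients, and Trial status says that results are already being analysed. It can only be offered as a description and must be labelled so.

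**The source trial.** A reader might also fault the planning effect because the Background describes its source as a telephone intervention with a "significant drop in non-adherence to medication and in the incidence of medication-related problems after a 4-week follow up". The Sample size section lists the alternatives considered and why they fitted less well. Taking the nearest available trial is a judgement, not an error, and is not part of this point.

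**Conclusion.** The point holds in a limited form. The article states 80% power for a comparison that is neither the definition of any primary outcome nor its confirmatory test, and the figure is not met for that comparison either: about 65% with 495 evaluable patients, against a requirement of about 875 enrolled (860 to 945 by formula, dividing by 0.8). The mismatch and the arithmetic rest on stated inputs alone, and confidence in them is high.

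The 0.25 to 0.29 SD figures assume that 619 are randomised, 20% are lost, the arms are about equal and a between-arm test is used. Whether differences of that size are plausible or important cannot be judged from the article. The defect is a stated property that the design does not have. It is not evidence that the trial is too small for its score outcomes.

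**What to change.** 1. In Statistical analysis, name a between-arm comparison of score change as the primary test, and keep the within-subject signed-rank results as descriptive.
2. In Sample size, replace the claim of 80% power with a dated statement, labelled as made after planning. Suggested text: *About 495 evaluable patients give 80% power at two-sided 5% to detect a between-arm difference of about 0.25 SD of the analysed variable (about 0.26 SD by Mann-Whitney) for each of GMAS, GRAS and RAKAS, or about 0.29 SD if alpha is split over the three.*
3. Say whether the SD is that of the score or of the change, and give point values only with a sourced SD.
4. Keep 16% versus 9% as background, or as a secondary comparison with a defined cut and its power restated as about 65%.

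The cost is two rewritten paragraphs, with no change to enrolment or data collection. Because results are already being analysed, the change in primary test must be disclosed with its date and timing relative to unblinding.

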### Trial design

This trial is designed as a randomized, single-blind, parallel group trial. It has two arms, i.e., a control or “usual care” arm and an intervention or “pharmaceutical care” arm. Patients would be recruited and randomly assigned to either of the two arms using a computer-generated list and the patients’ medical record numbers. The allocation ratio would be 1:1. The trial has been designed as per the Standard Protocol Items: Recommendations for Interventional Trials (SPIRIT) and Template for Intervention, Description and Replication (TIDieR) checklists which are available as Additional files 1 and 2.

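### The total of 619 patients does not give 80% power for 16% versus 9% nonadherence; after the planned 20% drop-out the power is about 65%

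*Protocol article*

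**What the plan says.** The protocol article's Sample size section bases the calculation on adherence, after a published trial of pharmacist advice. It gives all the inputs:

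- effect: "It was taken as a reduction in self-reported nonadherence from 16% to 9"%;
- type I error: "considering a (two-side) alpha value of 0.05", consistent with the Statistical analysis section, "The significance level will be set at 5% and a two-tailed test will be used";
- power: "statistical power of 80%, i.e., beta = 0.2";
- loss and result: "Considering a drop-out rate of 20%, we would require a total of 619 patients to successfully demonstrate a positive and statistically significant effect".

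The Trial design section adds that "The allocation ratio would be 1:1". The Statistical analysis section restricts the analysis to a per-protocol set of patients who completed the study, and names the chi-square test for comparing categorical variables between groups. No other design factor, such as a one-sided test or a gain from covariates, is given for the sample size.

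**The concern.** A fall from 16% to 9% is a difference of seven percentage points between two fairly low proportions. At two-sided 5% and 80% power this needs roughly 350 patients per arm, so a total of 619 that is said already to include 20% drop-out looks too small.

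This is the only sample-size justification in the article, and it is worded as an assurance that the trial can show the effect. If the power is overstated, a reader who meets a non-significant adherence result may take it as fairly strong evidence against the planned effect, when the design would miss that effect much more often than stated.

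**Working it through.** **Inputs** (Sample size and Trial design sections): p1 = 0.16, p2 = 0.09, difference 0.07, mean p = 0.125; two-sided alpha 0.05 (z = 1.96); power 80% (z = 0.8416); 1:1 allocation; drop-out 20%; stated total 619.

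**Attempt to reproduce 619.** Pooled-variance formula, per arm:

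n = [1.96·√(2·0.125·0.875) + 0.8416·√(0.16·0.84 + 0.09·0.91)]² / 0.07²
= [0.9167 + 0.3914]² / 0.0049 = 349.2, rounded up to 350.

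That is 700 evaluable patients and 700/0.8 = 875 enrolled. Other two-sided versions:

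| Method | Per arm | Evaluable total | Enrolled, total/0.8 | Enrolled, total×1.2 |
|---|---|---|---|---|
| Pooled | 350 | 700 | 875 | 840 |
| Unpooled | 347 | 694 | 868 | 833 |
| Arcsine | 344 | 688 | 860 | 826 |
| Continuity-corrected | 378 | 756 | 945 | 908 |

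Every evaluable total exceeds 619 before any allowance for drop-out, so the choice of inflation method cannot explain the figure.

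One-sided tests with 20% drop-out give 677–690 (total/0.8) or 650–662 (total×1.2) without continuity correction, and 722–758 with it. The nearest variant at the printed rates and power is one-sided, continuity-corrected and without drop-out (602–606). It contradicts both the stated two-sided alpha and the stated drop-out, and it still does not equal 619.

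**Power that 619 gives for 16% versus 9%.**

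Power = Φ{[0.07·√n − 1.96·√(2·0.125·0.875)] / √(0.16·0.84 + 0.09·0.91)}, where n is the number per arm.

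- No drop-out, n = 309.5: [1.2315 − 0.9167] / 0.4651 = 0.677, power 75.1%.
- 20% drop-out, 619 × 0.8 = 495, n = 247.5: [1.1012 − 0.9167] / 0.4651 = 0.397, power 65.4%.

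Exact enumeration of the Pearson chi-square test gives 75.6% at 310 per arm and 65.9% at 248 per arm. The unpooled and arcsine approximations at 495 give 65.8% and 66.2%.

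**Effect detectable with 80% power.** Solving the same power formula for p2 with p1 = 0.16 and 247.5 per arm gives p2 = 7.9%.

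**A possible origin (inference only).** For 16% versus 8% the pooled formula gives 257.8, so 258 per arm and 516 in total; 516 × 1.2 = 619.2. The total may therefore have been computed with 8%, using a 1.2 multiplier for drop-out. The document prints 9%.

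**The case against.** The strongest objection is that the total may be right and the printed rate wrong. The match for 16% versus 8% is close enough to make a misprint plausible, and the trial would then be near its nominal power for the effect intended. The source study cannot be consulted here, so this stays open. It does not remove the point: the printed rate and the printed total cannot both stand. Even on the 8% reading, multiplying by 1.2 under-allows for a 20% loss, and 495 completers give 78.4% power.

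A second objection is that the 65% belongs to a binary comparison, whereas the primary outcomes are changes in mean scores and the named confirmatory test is a within-subject Wilcoxon signed-rank test. That is correct and limits the claim. No standard deviation or score difference is given, so power for those analyses cannot be calculated from the document. But the plan chose the binary contrast to size the trial, and its 80% claim is about that contrast.

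Third, the achieved enrolment and drop-out are not reported, so 495 is a planning figure. This also stands, but the plan's own loss assumption and completer-only analysis set make it the planned analysed number. Keeping all 619 would still give only about 75%.

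Finally, the Trial status section says the trial is no longer recruiting and results are being analysed. That rules out a larger sample, but not a correction of the stated power.

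**Conclusion.** The sample size statement is wrong as written. For the printed inputs, 619 falls about 250 patients short of the 868–875 required (pooled and unpooled formulas, drop-out as total/0.8), and about 75–81 short even with no drop-out (694–700). Power for 16% versus 9% is 65–66% after the planned loss, so the risk of missing the planned effect is about 34–35% instead of 20%.

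This rests on 1:1 allocation, a two-sided 5% between-arm comparison of two proportions, and 20% loss with completers only analysed, all taken from the article. It says nothing about power for the score-based outcomes.

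**What to change.** Replace the conclusion of the Sample size section, and repeat the correction in the results paper, with wording such as: *With 619 patients enrolled and 495 evaluable after 20% drop-out, the trial has about 65% power to detect a reduction in nonadherence from 16% to 9% (two-sided 5%), and 80% power for a reduction from 16% to about 7.9%.* Remove the statement that 619 is enough for 80% power.

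While making the change, the authors should check the original calculation for the rate and drop-out method used. If 9% proves to be a misprint, say so and give the power for the intended rate with the drop-out divided out (495 evaluable).

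Interpret the between-arm difference in nonadherence by its confidence interval, so that a non-significant result is not read against a power the design did not have.

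The cost is one corrected paragraph in each document and a less favourable stated power. No further patients are enrolled.
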